#### Follow-up assessments

In addition to baseline assessment (M0), WEMWBS, CESAM, and EQ-5D are repeated before workshops five (beginning of the second month, M1), nine (beginning of the third month, M2), and twelve (end of the third month, M3) in the intervention and control groups. The week before the first, fifth, ninth, and twelfth workshops, all participants complete questionnaires alone at home using the CEEXLO web platform.

In the intervention group, participants complete the WEMWBS assessments while at the MMFA before and after the first, fifth, ninth, and twelfth workshops. In addition, before CESAM questionnaire completion, four additional questions with binary-coded answers (yes versus no) are asked: (1) Have you seen a physician since the last assessment? (2) If yes, was it a planned or unplanned visit? (3) Have you been hospitalized since the last assessment? (4) If yes, was it a planned or unplanned hospitalization?

Physiological measures are recorded in the intervention and control groups using the same schedule as the previous outcomes with 6 assessment times: M0, M1, M2, M3, as well as 6 and 12 months after the end of the intervention (M9 and M15). All participants who completed the initial 3-month intervention period are reassessed at M9 and M15. This follow-up assessment employs the same questionnaires as during the 3-month intervention. It is performed at participants’ place of living through the CEEXLO web platform with phone support, as needed. We minimize losses to follow-up by scheduling telephone interviews in advance or sending email reminders (for those who agree to this medium of communication).

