Museums have designed their spaces to create participatory art-based activity programs that can be carried out in a pleasant environment [8, 17–20]. For instance, in 2015, the Montreal Museum of Fine Arts (MMFA) developed “Thursdays at the Museum,” which is a participatory art-based activity performed by older community dwellers who live in Montreal creating art in group settings. In 2018, the effects of this participatory art-based activity on the well-being, quality of life, and frailty (i.e., physical health) of older community dwellers were examined [21]. With a pre-post intervention, single arm, prospective, and longitudinal design, we showed that the MMFA’s participatory art-based activity improved the well-being, quality of life, and frailty of older community dwellers in Montreal. Each outcome’s improvement evolved differently over the 3-month cycle of weekly art-based activities. Well-being was greater at the end of each workshop when compared to the beginning, with a similar magnitude of change throughout the cycle. In contrast, quality of life improved gradually over the course of the cycle. Finally, when comparing the cycle’s end to its beginning, the proportion of vigorous participants was greater, whereas the proportion of mildly frail participants was smaller. A major limitation of our first study was its design, as the gold standard to examine the effects of an intervention is a RCT in parallel groups.

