#### Randomization

After the baseline assessment, participants are randomly allocated to intervention and control groups using block randomization with a 1:1 ratio. The randomization list is established with the N’Query randomization software by the project manager, who is the only person able to identify participants based on their code. All investigators are blind to randomization. The project manager is not involved in the recruitment nor the follow-up of participants. He conducts the randomization process and informs the participants of to which group they are assigned. Randomization is performed the week before the first workshop.

Furthermore, a subset of participants is offered a Fitbit Alta HR (Fitbit, Inc.; San Francisco, CA, USA) to record physiological measures (i.e., heart rate, daily step count, sleep duration, and its phases). The subset is limited to 30 intervention group and 30 control group participants, determined in a second randomization that keeps the subsets as similar as possible to control for selection bias. This second randomization adopts the process used during the first randomization and the same project manager oversees it to ensure that all investigators remain blind. After the second randomization is completed, the project manager in charge of randomization provides selected participants with a Fitbit device, an assessment schedule and instructions. The project manager also installs the Fitbit application on participants’ portable electronic devices and creates their individual accounts with coded usernames.

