### Assessment

#### Baseline assessment

The baseline assessment is performed with all participants (intervention and control) during a first meeting in a dedicated room at the MMFA. It is a standardized interview performed by a representative of the principal investigator and is carried out before (M0) the first workshop, at the time when participants sign the written consent form. All measurement types and their times of use are shown in Table 1. All questionnaires and scales used are reliable and previously validated. No feedback on assessment results is shared with participants.

**Table 1 Tab1:** Assessed domains, instruments and time points

Domains	Instruments	Time points								
		Baseline (M0)		Follow-up						
		Before first workshop	After first workshop	M1		M2		M3		M9 and M15
				Before fifth workshop	After fifth workshop	Before ninth workshop	After ninth workshop	Before twelfth workshop	After twelfth workshop	
Ability to use a computer	CPQ	X								
Socio-demographic characteristics		X								X
Frail condition	CESAM	X		X		X			X	X
Well-being	WEMWBS	X	X	X	X	X	X	X	X	X
Quality of life	EQ-5D	X		X		X			X	X
Physiological measures		X		X		X			X	X
Physician consultation Emergency room visit and hospitalization		X		X		X			X	X

*M* month, *M0* baseline assessment, *M1* first month, *M2* second month, *M3* thrid month, *M9* 6 months after the end of the intervention, *M15* 12 months after the end of the intervention, *CPQ* computer proficiency questionnaire, *CESAM* Centre of Excellence Self-AdMinistered questionnaire, *WEMWBS* Warwick-Edinburgh Mental Well-being Scale, *EQ-5D* EuroQol-5D

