### Outcomes

The primary outcome is the change in WEMWBS score between the baseline assessment (M0) and the end of the 3-month cycle (M3), calculated using the formula ((score M^*n* + 1^ – score M^*n*^)/((score M^*n* + 1^ + score M^*n*^)/2)) × 100 [21, 26], expressed in percentage. Mean values and standard deviations will be used to define quantitative variables. The secondary outcomes are (1) the changes in WEMWBS scores between M0 and M1, M0 and M2, M0 and M9, and M0 and M15; (2) the mean WEMWBS scores before and after workshops in the intervention group at M0, M1, M2, and M3; (3) the changes in CESAM scores and its distribution of frailty categories (vigorous versus mild, moderate, and severe frailty) between M0 and M1, M0 and M2, M0 and M3, M0 and M9, and M0 and M15 [23]; (4) the change in EQ-5D scores, including VAS scores, between M0 and M1, M0 and M2, M0 and M3, M0 and M9, and M0 and M15 [25]; (5) the frequency of planned and unplanned physician visits, ER visits, and hospital admissions at M1, M2, M3, M9, and M15 [14, 16]; and (6) the changes in mean values of heart rate, daily steps, an sleep duration, and sleep phases, expressed in percentages, between M0 and M1, M0 and M2, and M0 and M3 for the subset of participants with recordings of these physiological measures. All changes will be expressed in percentages as mean values and standard deviations.

The number of workshops attended during the 3-month cycle of intervention is used to assess compliance with the participatory art-based activity. Compliance is defined as having attended at least 10 (83.3%) of the 12 workshops. If a participant attends a workshop for at least 1 h, they are considered to have attended a full workshop. If not, they are recorded as absent.

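### The text and Table 1 disagree on when M3 is scored, and only the intervention arm has post-workshop WEMWBS scores, so an acute workshop lift could enter the between-arm comparison

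*Protocol article*

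**What the plan says.** **Primary outcome (Outcomes).** "The primary outcome is the change in WEMWBS score between the baseline assessment (M0) and the end of the 3-month cycle (M3"), as a percent change. Neither the setting of the score nor its position relative to a workshop is given.

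**Home assessments, both arms (Follow-up assessments).** "The week before the first, fifth, ninth, and twelfth workshops, all participants complete questionnaires alone at home using the CEEXLO web platform". The same section has WEMWBS, CESAM and EQ-5D repeated before workshop "twelve (end of the third month, M3) in the intervention and control groups".

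**Museum assessments, intervention arm only (Follow-up assessments).** "In the intervention group, participants complete the WEMWBS assessments while at the MMFA before and after the first, fifth, ninth, and twelfth workshops".

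**Table 1 (Baseline assessment).** CESAM and EQ-5D are marked before the workshop at M0, M1 and M2, but at M3 only under "After twelfth workshop". WEMWBS is marked both before and after the workshop at M0, M1, M2 and M3. The table does not distinguish arms, and its M0 block includes a WEMWBS taken after the first workshop.

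**Baseline (Baseline assessment; Randomization).** "The baseline assessment is performed with all participants (intervention and control) during a first meeting in a dedicated room at the MMFA". Allocation follows this meeting: "Randomization is performed the week before the first workshop".

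**Earlier single-arm study (Background).** "Well-being was greater at the end of each workshop when compared to the beginning", by a similar amount throughout the cycle. The amount is not given.

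**Use stated for museum scores (Outcomes).** Secondary outcome (2) is the mean WEMWBS before and after workshops, within the intervention group.

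**The concern.** At M3 an intervention participant can hold three WEMWBS scores: at home in the preceding week, at the museum before workshop twelve, and at the museum after it. A control holds one, taken at home. The only M3 score shared by both arms precedes the last workshop, while the primary outcome is defined at the end of the cycle and Table 1 lists a post-workshop score under M3. An analyst working from Table 1 could take the post-workshop score for the intervention arm in good faith.

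That score would carry the immediate effect of having just left a workshop. Compared with a control's home score, it would mix a short-lived lift with the 3-month change that the trial sets out to measure, in an open-label trial with a self-reported endpoint.

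For CESAM and EQ-5D the conflict is sharper. Followed as written, Table 1 gives the intervention arm a pre-workshop M0 and a post-workshop M3. CESAM includes an item on mood that day and one on energy, and the EQ-5D VAS rates perceived health. The earlier study's lift is reported for well-being only; that these items share it is an inference.

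**Working it through.** **1. The M3 sources side by side**

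| Instrument | Follow-up assessments text | Table 1 |
|---|---|---|
| WEMWBS | Home, week before workshop 12, both arms; also at the museum before and after it, intervention arm | Before and after workshop 12, arms not separated |
| CESAM, EQ-5D | Home, week before workshop 12, both arms | After workshop 12 only |

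The CESAM and EQ-5D entries cannot both hold. The shift to the after column occurs in both rows, and only at M3, so it does not look like a text-extraction fault.

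**2. What each pairing does to the WEMWBS comparison**

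Let b be the acute lift on the percent-change scale. Controls contribute a home score at M3.

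| Intervention-arm M0 | Intervention-arm M3 | Bias between arms |
|---|---|---|
| Baseline interview | Home, week before workshop 12 | 0 |
| After workshop 1 | After workshop 12 | Largely cancels if the lift is similar at each workshop, as the Background reports |
| Baseline interview or before workshop 1 | After workshop 12 | About b in full |

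**3. Inputs for the size**

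Power calculation: SD 10.3, design difference 5.2, 63 per group. Data analysis: two-sided tests, final level 0.0498. The lift b is an assumption.

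The plan's own figure comes first. The normal-approximation formula n = 2(z₁₋α/₂ + z_power)² × SD² / difference², with alpha 5% and 90% power, gives 2 × (1.960 + 1.282)² × 10.3² / 5.2², or 83 per group. The stated 63 corresponds to about 80% power (62 by this formula, 63 with the t distribution). That is a separate matter. Here 63 serves only as an arm size, and 75 is shown beside it.

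**4. False-positive rate with no lasting effect and the third pairing**

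SE = 10.3 × √(2/n), which is 1.835 for n = 63 and 1.682 for n = 75. The critical value for 0.0498 is 1.962.

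Rate = Φ(b/SE − 1.962) + Φ(−b/SE − 1.962)

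For b = 1 and n = 63: Φ(0.545 − 1.962) + Φ(−0.545 − 1.962) = 0.0783 + 0.0061 = 0.084.

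| Assumed lift b (percentage points) | 63 per arm | 75 per arm |
|---|---|---|
| 0 | 5.0% | 5.0% |
| 1 | 8.4% | 9.1% |
| 2 | 19.3% | 22.1% |
| 3 | 37.2% | 42.9% |

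**5. What b means in scale points**

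With the plan's formula, a 1-point WEMWBS rise from an assumed baseline of 45 is 1/45.5 × 100 = 2.2, and from 55 it is 1/55.5 × 100 = 1.8. A lift of about one point on the 14 to 70 scale is therefore close to the b = 2 row.

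**The case against.** The strongest reply is that the design already contains the right comparison. The text labels the pre-workshop-twelve assessment M3 for both arms and places it at home for everyone. The museum scores have their own declared use in secondary outcome (2). No section directs a post-workshop score into the between-arm analysis, and the choice among several records at one time point is often left to an analysis plan, which is not shown here. For the primary outcome this stands to a large extent: a like-for-like home score exists, and the bias is conditional on a choice that the protocol does not make. It does not remove the conflict between Table 1 and the text, which is contradictory wording and not omitted detail.

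A reader might also infer three stronger things that the documents do not support:

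- **That controls are scored only at home at M0 as well.** Both arms have the baseline interview at the museum, before randomization, and the primary outcome refers to that baseline assessment. The extra home questionnaire in the week before workshop one and the post-first-workshop column are untidy, but the Outcomes section names neither as baseline.
- **That most null trials would come out positive.** Setting b to 5.2 gives about 81%, but this equates the lift with the whole design effect and only restates the power at 63 per arm. Nothing in the documents supports a lift of that size.
- **That M3 must move to after workshop twelve.** The text itself calls the earlier assessment the end of the third month. The first participant was recruited in March 2019, so a move could put participants on different schedules.

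**Conclusion.** The point holds for M3. Table 1 and the Follow-up assessments section contradict each other on the timing of CESAM and EQ-5D. Table 1 also lists a post-workshop WEMWBS under M3 without saying that it exists for one arm only, and the Outcomes section does not settle which score is primary.

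The effect on the primary comparison ranges from none (home scores in both arms) to the full acute lift (baseline or pre-workshop M0 with post-workshop M3 in the intervention arm). In that worst case, a lift of 1, 2 or 3 percentage points gives a false-positive rate of about 8%, 19% or 37% at 63 per arm. These figures assume no lasting effect, SD 10.3 in both arms and a normal approximation. The lift sizes are assumptions; the documents give only the direction. For CESAM and EQ-5D the unequal timing follows directly from Table 1, but any lift in those scores is inferred.

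**What to change.** State, before any between-arm analysis, that all such comparisons use in both arms:

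- **M0:** the score from the pre-randomization baseline interview. The week-before-workshop-one home score should not serve, since randomization falls in that same week and participants may already know their group.
- **M3:** the home web-platform score completed in the same calendar week in both arms.

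The change of setting from interview to home is then common to both arms. The same home rule can cover M1 and M2, where Table 1 also marks WEMWBS on both sides of the workshop.

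Then reconcile Table 1 with the text so that M3 CESAM and EQ-5D come from that home assessment, show which WEMWBS entries apply to the intervention arm only, exclude the post-first-workshop WEMWBS from the baseline used for change scores, and reserve the on-site scores for secondary outcome (2).

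The cost is a few sentences and a corrected table, with no new visit and no change to assessment timing. The one small downside is that the M3 score precedes the last session, so it reflects 11 of the 12 workshops; the protocol should say so.

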Findings from our first study suggest that “Thursdays at the Museum” may improve older adults’ mental (i.e., well-being and quality of life) and physical (i.e., frailty) health. The relationship between well-being, quality of life, and physical health is complex. Previous studies, including our first study, suggested the existence of a chronological sequence of benefits: positive experiences induced by art-based activities improve well-being, which improves quality of life and, finally, physical health [6–13, 21]. This sequence may explain the changes in outcomes over time reported in our first study. However, the changes in well-being, quality of life, and physical health that older community dwellers experience over time and independently of any intervention are sparsely known. These aging-related changes may influence the effects specific to “Thursdays at the Museum.” We hypothesize that changes in well-being, quality of life, and frailty due to older community dwellers’ participation in “Thursdays at the Museum” (1) each have not the same profile of evolution over time; (2) are greater than those observed with aging (i.e., experienced by the older adults with or without morbidities that make up the control group); (3) are improvements of well-being, quality of life, and frailty; and (4) may persist after the discontinuation of “Thursdays at the Museum.”

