### Power calculation

The number of participants required for this study has been calculated to detect the expected change in WEMWBS score between the baseline assessment (M0) and the end of the 3-month cycle (M3) calculated using the formula ((score M^*n* + 1^ – score M^*n*^)/((score M^*n* + 1^ + score M^*n*^)/2)) × 100. The expected difference between intervention and control group was estimated 5.2 ± 10.3 based on a previous study [21]. A free sample size calculator (http://www.sample-size.net/sample-size-means/) was used*.* The minimum number of participants to show an absolute difference between the 2 groups (i.e., intervention and control groups) with alpha = 5% and power = 90% is of 63 per group. Thus, the theoretical total number of participants for the study is 126. Anticipating an 18% rate of participant loss during the follow-up period, the total number of participants required is 150 (75 participants per group).

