### Data analysis

Analyses will be performed (1) with the intention to treat for all enrolled participants randomized into two groups (i.e., intervention versus control) and (2) per protocol (i.e., removing data from participants who were not compliant with the protocol) for participants who will be entirely assessed through an 83.3% (i.e., participants who attended 10 on 12 workshops) compliance to the intervention. Analyses will be done through the SPSS Software (version 23.0; SPSS, Inc., Chicago, IL). Missing data will be taken into account with regression imputation. Data will be imputed only if the percentage of participants with missing data is under 10%. The continuous variables’ distributions will be studied (mean, median, mode, minimum, maximum, confidence interval around mean, standard deviation). For the categorical variables, frequencies will be calculated. First, the participants’ baseline characteristics (age, sex, etc.) will be described for each group and compared (i.e., intervention versus control) using parametric and non-parametric tests according to variables’ distribution. Pearson’s chi-square tests (or Fisher’s exact tests) will be used for qualitative variables. For quantitative variables, the statistical tests used will be unpaired *t* tests or non-parametric Mann-Whitney *U* tests for comparing 2 groups, as appropriate.

Second, group comparisons of changes (i.e., ((score M^*n* + 1^ – score M^*n*^)/((score M^*n* + 1^ + score M^*n*^)/2)) × 100) in outcome values between M0 and M1, M0 and M2, M0 and M3, M0 and M9, and M0 and M15 will be performed using repeated measures tests as appropriate. The global significance limit will be set at 0.05 and all tests will be bilateral. In addition to this univariate analysis, a multivariate analysis will be performed to determine the effect of the intervention while adjusting for age, sex, number of medications taken daily, and CPQ score. These adjusted variables are covariates that may influence the relationship between outcome measures (i.e., well-being, quality of life, and frailty) and the participatory art-based activity intervention.

Third, to identify the outcomes with the highest magnitudes of change (i.e., greater effect attributable to the intervention), we will graph the mean difference of each outcome that is significantly different when comparing intervention group participants to those in the control group. Results will be presented as forest plots.

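### Reassessment at M9 and M15 is tied to completing the first three months, which conflicts with the intention-to-treat comparison promised at those visits

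*Protocol article*

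**What the plan says.** The Follow-up assessments section fixes who is seen after the programme ends: "All participants who completed the initial 3-month intervention period are reassessed at M9 and M15". These visits are questionnaires answered at home on the web platform, with telephone help if needed.

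The Data analysis section sets the main analysis population as "with the intention to treat for all enrolled participants randomized into two groups". Its list of group comparisons runs through the two late time points: "and M0 and M15 will be performed using repeated measures tests as appropriate".

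The late visits carry a stated hypothesis. The Background expects that benefits "may persist after the discontinuation of" the programme. The Outcomes section lists the matching secondary outcomes, for example "the changes in WEMWBS scores between M0 and M1, M0 and M2, M0 and M9, and M0 and M15". It lists the same late time points for frailty, quality of life and health-care use.

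Two further statements bear on the consequence. On missing data: "Data will be imputed only if the percentage of participants with missing data is under 10" per cent. On expected attrition, in the Power calculation: "Anticipating an 18% rate of participant loss during the follow-up period".

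**The concern.** Eligibility for the M9 and M15 visits depends on something that happens after allocation. A randomised person who stops before the three-month point is not scheduled for either visit, so the late outcome is missing by design and not only because the person could not be reached. The analysis section nevertheless treats the late comparisons as intention-to-treat comparisons of the full randomised groups.

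What is at stake is the persistence question. If people who stop early differ in outcome from those who stay, and stopping is not alike in the two arms, the late difference mixes the effect of the programme with the effect of selection. A data-collection rule is hard to repair afterwards, since an analysis cannot supply observations that were never sought.

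**Working it through.** **1. The two rules side by side**

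| Item | Follow-up assessments | Data analysis |
|---|---|---|
| Who | those who completed the first three months | everyone randomised |
| When | M9 and M15 | M1, M2, M3, M9 and M15, each against M0 |

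The Setting and recruitment section says that information on people who drop out is recorded, but it promises no outcome assessment for them. Nothing else in the article fills the gap.

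**2. What completion could mean**

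- *Still assessed at M3.* One rule for both arms, but still a post-randomisation condition. The set is the randomised set minus early leavers.
- *Workshops finished.* Only the intervention arm has workshops, so the condition differs by arm as well as being post-randomisation.

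Neither meaning returns the randomised groups.

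**3. Would the missing-data rule help?**

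Inputs: 150 randomised, 18% loss (Power calculation) and the 10% ceiling (Data analysis). The plan's step from 126 to 150 is roughly consistent with 18% (126 × 1.18 = 148.7; 126 / 0.82 = 153.7). The present point does not depend on it.

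- Ceiling: 0.10 × 150 = 15, so imputation is used only with fewer than 15 people affected.
- Expected loss: 0.18 × 150 = 27, leaving 150 − 27 = 123.

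As 27 exceeds 15, imputation would not be used at the plan's own expected loss. The documents do not say how much of the loss falls before M3. If all of it did, about 27 people would never be approached at M9 or M15; if less, fewer.

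**4. Size of the possible bias**

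Let d1 and d2 be the proportions not completing in the intervention and control arms, and g the mean change in completers minus that in non-completers. In each arm, the mean over all randomised = completer mean − d × g. With the same g in both arms:

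completer difference − full-population difference = (d1 − d2) × g

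The documents give neither d1, d2 nor g. I assume g = 5.2 or 10.3, the difference and the spread quoted in the Power calculation, purely to set a scale. For the false-positive risk I take SD = 10.3, no true effect, n = 75 × (1 − d) per arm, SE = 10.3 × √(1/n1 + 1/n2), and risk = 1 − Φ(1.96 − bias/SE) + Φ(−1.96 − bias/SE).

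| d1 vs d2 | g | Bias (percentage points) | Two-sided false-positive risk |
|---|---|---|---|
| 18% vs 18% | 5.2 or 10.3 | 0 | 5.0% |
| 18% vs 9% | 5.2 | 0.09 × 5.2 = 0.47 | 5.8% |
| 18% vs 9% | 10.3 | 0.09 × 10.3 = 0.93 | 8.1% |
| 27% vs 9% | 5.2 | 0.18 × 5.2 = 0.94 | 7.9% |
| 27% vs 9% | 10.3 | 0.18 × 10.3 = 1.85 | 16.8% |

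The sign reverses if controls leave more often, or if those who leave do better than those who stay.

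**The case against.** The strongest reply is that the sentence describes ordinary retention: people still in the study at three months are followed up, in both arms, by one rule. Attendance has its own term, since "Compliance is defined as having attended at least 10 (83.3%) of the 12 workshops", and the follow-up sentence does not use it. The abstract lists six assessment occasions and Table 1 has M9 and M15 columns, neither with a filter. The article is condensed, and its flow chart is not visible here. Many early leavers would have withdrawn consent or be out of reach anyway, so the rule itself costs only those who stopped but would still have answered. A repeated-measures model that uses all available data could also draw on their earlier visits. Only secondary outcomes are touched.

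Much of this stands, and it limits the point. A reader might infer that people who attended all 12 workshops will be compared with controls who met a much weaker condition, and that the late results are therefore tilted towards the intervention. The documents do not support that: completion is undefined, the workshop meaning is only one possibility, and the direction of selection is unknown.

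A reader might also put the overstatement at 0.18 × 5.15 = 0.93 points, or 18% of the planned 5.2. That assumes selection in the intervention arm only, non-completers half an SD worse, and full recovery of the lost data. It also borrows a benchmark set for M0–M3, since no effect is planned for M9 or M15.

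What does not stand is that the conflict disappears. Even on the retention reading, randomised people who left early but still consent are not scheduled for M9 or M15. The repeated-measures method is not specified, and a model could replace their late values only by assumption.

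**Conclusion.** The point holds as an internal conflict: the follow-up rule does not deliver the population that the analysis section promises for M0–M9 and M0–M15. This is true on either meaning of completion. At the plan's own 18% loss the imputation provision falls away, and the persistence comparisons would rest on completers.

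The size and direction of any bias are unknown. The range includes zero (balanced non-completion with an equal gap in both arms) and reaches about 0.5 to 0.9 points at an assumed 18% versus 9%. The wider 27% versus 9% case, also an assumption, gives about 0.9 to 1.9 points. All these figures compare the rule with complete follow-up, so they are upper limits on what the fix could recover in each scenario.

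The primary M0–M3 outcome is not affected by this sentence. Severity is moderate, confined to secondary outcomes.

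**What to change.** Replace the sentence in Follow-up assessments with one to this effect: *every randomised participant who has not withdrawn consent is approached at M9 and M15, whatever their workshop attendance and whether or not they were assessed at M3.* This also removes the need to define completion for the purpose of follow-up.

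For participants whose late visits have already passed without contact, describe the M9 and M15 results as a completers analysis, not as intention to treat, and report by arm how many randomised people were not approached.

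The cost is a small amendment plus some extra questionnaire links and reminder calls on the existing platform. If all 27 expected losses fell before M3, that is at most 27 × 2 = 54 additional questionnaires. The trial is described as ongoing, so the change is worth making early; visits not offered cannot be recovered.
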